## Abstract

**Background:**

Excess dietary salt is a leading risk for health. Multiple health, government, industry and community organisations have identified the need to reduce consumption of dietary salt. This project seeks to implement and evaluate a community-based salt reduction intervention.

**Methods:**

The study comprises a baseline assessment followed by a targeted intervention and then an evaluation of efficacy. The study location is Lithgow, a regional town in New South Wales, Australia. The salt reduction intervention is based upon the Communication for Behavioural Impact framework which utilises an integrated communication model to enact community advocacy and impact by providing tools that enable the translation of knowledge into behavioural change. The duration of the intervention will be between 6 and 12 months. The primary evaluation will be through measurement of 24-hr urinary sodium excretion in independent population samples aged > 20 years, drawn before and after the intervention period. The study is designed to detect a difference in mean sodium excretion of 0.7 grams per day or greater with 80% power and p = 0.05.

**Discussion:**

This study will provide a robust evaluation of the effectiveness of a community-based intervention seeking to reduce dietary salt intake using the Communication for Behavioural Impact framework. The results will provide important new evidence to inform the design and implementation of current and future salt reduction policies in Australia. The results will also have important international implications because, following the recent World Health Organization recommendations for the control of non-communicable diseases, many countries are now seeking to achieve a reduction in average population salt consumption.

**Trial registration:**

ClinicalTrials.gov, NCT02105727

## Background

The global burden and threat of non-communicable disease (NCDs) creates a major public health challenge that undermines social and economic development throughout the world [1]*.* In 2008 an estimated 63 per cent (36 million) of all global deaths were due to NCDs, comprising mostly cardiovascular diseases [2]. In Australia, cardiovascular disease is the leading cause of death and disability and the number one cost to the health sector [3,4]. There is clear evidence that a diet high in salt is associated with increased blood pressure, and that increased blood pressure leads to increased risk of vascular diseases [5]. Whilst there is no definitive estimate of population dietary salt intake in Australia, it is widely accepted that average consumption is between 7 and 12 g/day [6]; this is far above the suggested dietary target for Australians of 4 g/day [7].

The reduction of salt intake and sodium content of food has been recommended as a cost effective action that should be undertaken immediately, with expected accelerated results in terms of lives saved, cases of disease prevented and costs avoided [8]. As such, salt reduction activities are being promoted worldwide as a core component of efforts to achieve a 25 per cent reduction in avoidable NCDs by the year 2025. Specifically, the goal is to achieve a 30 per cent reduction in average salt consumption by 2025 [9]. The current Australian approach to reducing population salt intake is based upon voluntary food supply reformulation [10]. Community-based approaches may also be of value, especially those which place strong emphasis on behaviour impact by providing tools that enable the translation of knowledge into behavioural change [11].

In this study, two tools which may assist consumers to reduce salt consumption were identified. The first is a sodium-reduced salt substitute. Not only because a salt substitute might have an important effect on salt intake for individuals using alarge amount of discretionary salt, but also because it offers a talking point for consumers to engage around. The second tool, *“FoodSwitch”*, addresses the primary contributor to salt in the diet; processed foods. This electronic tool empowers consumers to choose healthier, lower salt versions, of food types they enjoy by providing specific advice about which products to pick from the supermarket shelves.

## Methods

The project involves a baseline assessment, followed by a targeted intervention and an evaluation of efficacy. The study is being conducted in Lithgow, a regional town with a residential population of about 20,160 [12] located 140 kilometres west of Sydney, New South Wales, Australia. Work commenced in 2010 and the evaluation will conclude with surveys done in 2014.

### Study aims

The primary objective of this study is to determine the effect of a multi-faceted community-based salt reduction intervention on mean salt intake, as estimated from measures of 24-hr urinary sodium excretion made before and after the intervention is implemented. The null hypothesis to be tested is that there will be no change in sodium excretion.

The secondary objectives are to determine the effects of the salt reduction intervention, by comparing measures before and after the intervention, on (1) population knowledge, attitudes and behaviour toward salt intake and (2) the sources of sodium in the diet, as estimated from 24-hr dietary recalls.

Exploratory objectives will be to examine (1) social inclusion as a determinant of response to the intervention; (2) the potential for a volunteer sample to provide estimates of population salt consumption and changes in population salt consumption; (3) whether spot urine samples can provide estimates of population salt consumption and changes in population salt consumption and (4) the association between urinary iodine excretion and urinary sodium excretion in females aged 20–45 years.

### Participant selection and recruitment

In this study we intend to recruit two samples of individuals at baseline, a randomly selected sample and a volunteer sample. At follow up we will invite those same participants that participated at baseline, as well as recruiting an additional randomly selected sample and a new volunteer sample (Figure 1).

**Figure 1 F1:**
[figure not shown]
Project design.

*For the random sample*, at baseline the electoral roll will be used to obtain the name and address of each potential participant with electronic databases searched to identify corresponding telephone numbers. At follow up a random sample will be selected from the local telephone directory. Potential participants will be first mailed invitations to take part in the survey, with an explanation of the purpose of the study, a participant information sheet and a consent form provided. These individuals will then be contacted by telephone to determine their willingness to participate and to schedule an interview time. Where a telephone number cannot be obtained, the home address will be visited by a member of the research team to determine willingness to participate.

*The volunteer sample* will be recruited by offering participation in the study to individuals at two local shopping centres, workplaces and community events. An information booth will be set up where those interested can seek further information about participation and arrange a visit by a member of the study team.

*Re-sampling of the participants included at baseline* will be done by verifying participants are still residents of Lithgow using electronic databases and then mailing invitations to take part in the follow up survey in the same way that we did for initial sampling.

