### Participant inclusion and exclusion criteria

All adults over the age of 20 years residing in the Lithgow area are eligible, with no exclusion based on inter-current illness, use of medications or any other aspect of demography or personal history.

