### The salt reduction intervention

The goal of the intervention is to reduce salt consumption amongst adults residing in Lithgow. The means by which this will be achieved is through the application of the Communication for Behavioural Impact framework which utilises an integrated communication model to enact community advocacy and impact [17]. There are five broad components to this approach:

1. *Administrative mobilisation and public advocacy* – for putting salt reduction on the agenda of all doctors and nurses, allied health professional and local government staff via engagement through a series of meetings. The desired outcome is for these professionals to advocate for salt reduction within the community.

2. *Community mobilisation –* Businesses, workplaces and school settings will be engaged through meetings, presentations and the provision of the tools to enact salt reduction.

3. *Advertising* – Local channels of communication including newspapers, social media and radio will be targeted with stories about the program. A series of specific advertising initiatives involving local and social media will be scheduled over the period of the intervention.

4. *Interpersonal communication –* information booths will be established in the two main shopping areas and by door knocking individual homes. The tools will be supplied to support interpersonal communication and engagement across the community. These tools will support one-on-one interactions with the community and enable conversations about the importance of reducing salt consumption as well as providing practical ways to achieve a reduction. (see the ‘key messages for intervention’ subsection).

5. *Point of Service/Sale –* the salt substitute has been made available at local cafes and restaurants for use by consumers. Local bakeries have also been provided with the salt substitute to use in baking. Government buildings, medical centres and pharmacies are also stocked with the salt substitute to enable consumers to obtain and replace the salt substitute at no cost.

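### The random sample comes from the electoral roll at baseline but from the telephone directory at follow-up, so within the random-sample contrast sampling frame and survey wave are confounded, and this enters the pooled primary estimate

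*Protocol article*

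**What the plan says.** The text under Figure 1, in the Participant selection and recruitment section, names a different frame for each survey. For the first, "at baseline the electoral roll will be used to obtain the name and address of each potential participant", and telephone numbers are then looked up in electronic databases. For the second, "At follow up a random sample will be selected from the local telephone directory". No reason for the change is given.

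The contact steps (mailed invitation, telephone call, home visit) are described once, without being limited to either survey. The last of them reads: "Where a telephone number cannot be obtained, the home address will be visited by a member of the research team".

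The target population is the same at both waves: "All adults over the age of 20 years residing in the Lithgow area are eligible". The abstract describes the primary evaluation as "24-hr urinary sodium excretion in independent population samples aged > 20 years, drawn before and after the intervention period". The follow-up survey has other components as well: "At follow up we will invite those same participants that participated at baseline, as well as recruiting an additional randomly selected sample", together with a new volunteer sample.

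The Data analysis section forms the primary comparison by fixed-effect pooling of the sub-set effects with inverse-variance weights. It analyses the volunteer, random and paired samples separately as subsidiary analyses. Covariates enter only if the two waves are found to differ in age, sex or body mass index, and only those three are named.

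**The concern.** There is no control town, so the intervention effect is read entirely from the difference between the two waves. That reading requires both waves to represent the same population. In the random-sample contrast, all baseline participants come from the roll and all newly drawn follow-up participants from the directory. If adults who can be found in the directory differ in salt intake from adults on the roll, the difference appears as a change over time. It could mimic an intervention effect or hide one. A larger sample does not remove it.

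More than one line of results is at stake. The random-sample contrast contributes to the pooled primary estimate. It is also the natural benchmark for the exploratory objective on whether a volunteer sample can measure change in population salt consumption.

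**Working it through.** **1. Which adults each procedure can reach**

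| Resident | Baseline (roll) | Follow-up (directory) |
|---|---|---|
| On the roll, number found | Selectable, contacted by telephone | Selectable if listed in the directory |
| On the roll, number not found | Selectable, reached by home visit | Not selectable if unlisted |

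The home visit acts on people who have already been selected. With the roll as frame it keeps people without a findable number. With the directory as frame, unlisted people were never selected, so it cannot recover them.

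**2. What the planned adjustment covers**

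If triggered, it handles shifts in age, sex and body mass index. It does not cover listing status, tenure or social position, although the questionnaire records socio-demographic variables. The Data collection section's assurance that procedures are the same at both waves concerns measurement, not sampling.

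**3. The plan's own power figures**

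The Sample size section gives 600 individuals, more than 80% power for 0.7 g/day salt and more than 95% for 1.0 g/day. It states no standard deviation, so neither figure can be independently reproduced. Solving for the largest standard deviation that gives 80% power at 0.7 g, with two-sided 0.05 (sidedness assumed) and a normal approximation:

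- 300 per wave: 0.7 / (2.802 × √(2/300)) = 3.06 g/day
- 600 per wave: 0.7 / (2.802 × √(2/600)) = 4.33 g/day

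At either limit the power for 1.0 g is 97.9%, so the two statements agree with each other. The implied standard error at exactly 80% power is 0.7 / (1.960 + 0.842) = 0.250 g/day, whichever way 600 is read.

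**4. Effect of a residual frame shift on the pooled estimate (assumed values)**

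The document gives neither the residual shift *d* nor the weight *w* of the random subset, so both are assumed. The standard error of the pooled estimate is taken as 0.250.

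- Pooled bias: b = w × d
- False-positive rate with no true change: Φ(b/SE − 1.96) + Φ(−b/SE − 1.96)
- Power for a true 0.7 g reduction if the bias works against it: Φ((0.7 − b)/SE − 1.96)

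| w | d (g/day) | b (g/day) | False-positive rate | Power if opposed |
|---|---|---|---|---|
| 1/3 | 0.2 | 0.067 | 5.8% | 72% |
| 1/3 | 0.35 | 0.117 | 7.5% | 65% |
| 1/3 | 0.5 | 0.167 | 10.2% | 57% |
| 1/2 | 0.2 | 0.10 | 6.9% | 67% |
| 1/2 | 0.35 | 0.175 | 10.8% | 56% |
| 1/2 | 0.5 | 0.25 | 17.0% | 44% |

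For the last row: 0.25/0.250 = 1.0, and Φ(−0.96) + Φ(−2.96) ≈ 0.169 + 0.002 = 0.17.

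**The case against.** The strongest defence is that the plan already contains much of the protection.

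- **Pooling and separate reporting.** The paired sub-set compares the same people, and the volunteer contrast uses neither frame. The three samples are also analysed separately, so a discordant random-sample result would be visible. This stands: it limits the confounding to one component and dilutes it, but does not remove it from the primary estimate.
- **Adjustment.** A reader might illustrate the bias with a directory sample that has 10 points fewer men and is 5 years older. At an assumed 2 g/day for sex and −0.02 g per year of age, this gives −0.10 × 2 + 5 × (−0.02) = −0.30 g/day. But these are shifts that the plan adjusts for once detected. With an assumed age standard deviation of 15 years and 150 to 300 random participants per wave, a 5-year shift gives z = 5 / (15 × √(2/n)), or 2.9 to 4.1, so detection is very likely. Under linear effects the illustrated bias would then largely vanish. What remains is the part that those covariates do not capture.
- **Dilution.** Applying −0.30 g to the whole comparison gives 0.30/0.25 = 1.2 and a rejection rate of about 22%. That ignores the pooling. With an assumed 15% to 40% of the weight, the pooled bias is 0.045 to 0.12 g/day and the rate is about 5.4% to 7.7%, even before adjustment.
- **Inferred mechanisms.** One might infer that the sampling unit moves from persons to listed households, or that the home visit never operates at follow-up. The article does not describe within-household selection and states the contact steps once for both waves. Neither inference is needed for the point.

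A reader might also infer that follow-up volunteers are selected for exposure to the intervention. Volunteers are sought among "individuals at two local shopping centres, workplaces and community events", while for the intervention "information booths will be established in the two main shopping areas" and workplaces are engaged. The Project status section shows that the periods overlap in the first half of 2014. But one volunteer method is described for both waves, and nothing says that volunteers are recruited at intervention booths. Greater exposure is possible, not established.

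**Conclusion.** The point holds for the random-sample contrast. The frame differs between waves, the two frames do not reach the same adults, and the planned covariates cannot be relied on to remove the difference. The confounding reaches the primary result only through the weight of the random subset in the pooled estimate. The document does not support saying that the whole before-after difference is confounded with the frame.

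The size and direction of the residual bias cannot be derived from the document. The range of about 6% to 17% false positives rests on three assumptions: a residual shift of 0.2 to 0.5 g/day, one-third to one-half of the weight, and a pooled standard error of 0.25 g/day. If the shift opposes a true 0.7 g reduction, power falls from 80% to between 72% and 44% over the same range. The change should be made, since the article places the follow-up survey in the future. The possible difference in volunteers' exposure is secondary.

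**What to change.** **Preferred.** Draw the follow-up random sample from the current electoral roll, with the same number search and home-visit steps as at baseline. This costs a new roll extract and the home visits, and it depends on the roll being obtainable, on which the article is silent.

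**If the roll cannot be obtained**, state why and pre-specify:

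- (a) adjustment of the random-sample contrast for age, sex, body mass index and the socio-demographic variables already collected, whether or not a difference test is positive, or standardisation of both waves to the same population margins;
- (b) a sensitivity analysis restricting baseline random participants to those listed in the local telephone directory. Those whose number was found in the database search are only an approximation, because the databases need not match the directory;
- (c) the pooled primary estimate with and without the random subset, shown beside the paired result.

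This fallback costs some analysis time and leaves fewer baseline participants in the sensitivity analysis. It also needs the baseline listing status or search results to have been kept.

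**Volunteers.** Record each volunteer's recruitment site. Compare intervention reach between volunteers and the random sample, using the reach questions already planned for the follow-up survey. The added cost is small.

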### Data analysis

The characteristics of the full baseline and follow up samples will be summarised and compared, as will the characteristics of the volunteers, those selected at random and those for which paired baseline and follow-up specimens are available.

For each individual, the 24-hr sodium excretion value (mmol/day) will be calculated as the concentration of sodium in the spot urine (mmol/L), multiplied by the spot urine volume (L/day) added to the concentration of sodium in the remaining urine (mmol/L) multiplied by the volume of the remaining urine (L/day). The conversion from mmol to grams will be made by dividing by 17 and the conversion from sodium (Na) to salt (NaCl) by multiplying by 2.542.

The primary comparison between baseline and follow-up levels of 24-hr urinary sodium excretion will be made using an inverse-variance weighted fixed effect pooled estimate of the effects in the sub-sets of participants. The primary analysis will be supplemented by subsidiary analyses that separately explore the baseline and follow-up differences for 1) the volunteer sample, 2) the random sample and 3) the sample for which both baseline and follow-up specimens are available. Differences will be tested using t-tests and paired t-tests. The analysis will be unadjusted unless there is evidence that the baseline and follow-up samples differ in regard to age, sex or body mass index, in which case these covariates will be included in the models.

Bland-Altman plots will be used to explore the agreement between spot urine and 24-hr urine collections, and to determine whether the agreement between the two methods of collection varies across different levels of sodium excretion.

Daily iodine intake will be estimated by multiplying the concentration of iodine in the urine measured in μg/l by 0.0235 and by body weight measured in kilograms [20]. Urinary iodine status data will be summarised as median urinary iodine excretion values and the proportions with iodine deficiency and iodine sufficiency according to the World Health Organization and the International Committee on the Control of Iodine Deficiency Disorders (ICCIDD) [21]. Mann–Whitney U tests will be used to compare differences in urinary iodine excretion according to World Health Organization urinary salt excretion target of ≥ 5 g/day and < 5 g/day, while general linear models will be used to investigate the continuous association between iodine and sodium excretion.

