### Project status

The baseline community assessment was undertaken in the first and second quarters of 2011 and the follow-up assessment will be done in the first and second quarters of 2014. The intervention will be implemented from the third quarter of 2013 to the second quarter of 2014. The findings of the baseline assessment were used to inform the design of the community-based salt reduction intervention.

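### New volunteers at follow-up are recruited through the same types of venue that deliver the intervention, while it is still running, so the volunteer contrast and the pooled primary estimate may overstate the community effect

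*Protocol article*

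**What the plan says.** **Recruitment.** Under Participant selection and recruitment, a new volunteer sample is taken at follow-up in addition to the one at baseline. Volunteers "will be recruited by offering participation in the study to individuals at two local shopping centres, workplaces and community events". The device is a booth: "An information booth will be set up where those interested can seek further information about participation". No different rule is given for follow-up.

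**Delivery.** Under The salt reduction intervention, component 4 states that "information booths will be established in the two main shopping areas and by door knocking individual homes", with the tools supplied to support these contacts. Component 2 states: "Businesses, workplaces and school settings will be engaged through meetings, presentations and the provision of the tools to enact salt reduction". Other channels reach the whole town, for example component 3: "Local channels of communication including newspapers, social media and radio will be targeted with stories about the program".

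**Timing.** Project status places baseline in the first half of 2011 and the intervention from the third quarter of 2013 to the second quarter of 2014. It adds that "the follow-up assessment will be done in the first and second quarters of 2014".

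**Analysis.** The primary comparison is an "inverse-variance weighted fixed effect pooled estimate of the effects in the sub-sets of participants" (Data analysis). The volunteer, random and paired samples are analysed separately only as subsidiary analyses. The only covariates named are age, sex and BMI, used if the samples differ on them.

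**Objective 2.** Study aims lists as exploratory "the potential for a volunteer sample to provide estimates of population salt consumption and changes in population salt consumption".

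**The concern.** Recruitment and delivery share venue types and a device, and the plan separates them neither in place nor in time. In 2011 a volunteer met at a shopping centre or workplace could not have met the intervention there. In 2014 the volunteer could, and the urine collection follows the study visit by 3 to 10 days, so such contact would come before the outcome is measured. Being recruited and being exposed can thus be linked in one survey and not in the other. Adjustment for age, sex and BMI does not remove that link.

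Two results are at stake. The primary objective is the effect on mean salt intake in the community. A sub-set that over-represents people reached by the programme would move the pooled estimate towards the effect in those people. For objective 2, a difference in change between volunteers and the random sample could reflect volunteering, exposure at the recruitment venue, or both.

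**Working it through.** **1. Do recruitment and delivery overlap?**

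| | Volunteer recruitment | Intervention delivery |
|---|---|---|
| Shopping | two local centres | two main shopping areas |
| Device | information booth | information booth |
| Workplaces | yes | yes |
| Community events | yes | not listed |
| Town-wide channels | none | media, door knocking, cafes, bakeries, pharmacies, medical centres, government buildings |
| Active in first half of 2014 | yes (follow-up) | yes |

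The overlap in venue type, device and calendar time is in the text. Identity of sites is not.

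**2. The plan's own figure.** The Sample size section states more than 80% power for 0.7 g/day salt and more than 95% for 1.0 g/day, with 600 individuals. It gives no SD, so the figure can only be inverted. With two-sided alpha 0.05 (assumed) and two equal independent samples of n:

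largest SD = difference / [(z for alpha + z for power) × √(2/n)]

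- 600 per survey: 0.7 / (2.802 × 0.0577) = 4.33 and 1.0 / (3.605 × 0.0577) = 4.80 g/day.
- 300 per survey (600 in total): 0.7 / (2.802 × 0.0816) = 3.06 and 1.0 / (3.605 × 0.0816) = 3.40 g/day.

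Either reading can be met by a suitable SD, so the power statement is neither confirmed nor refuted. It serves here only as the source of the 0.7 g/day yardstick.

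**3. How large could the bias be?** Let w be the volunteer contrast's weight in the pool, d the share of follow-up volunteers exposed minus the share exposed in the town, and e the mean reduction in those exposed. If the other sub-sets have the town's exposure:

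- bias in the volunteer contrast = d × e
- bias in the pooled estimate = w × d × e

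The article gives none of the three. The ranges are assumptions: w from 0.20 to 0.50, d from 0.10 to 0.50, e from 0.7 to 1.0 g/day salt.

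| Case | w | d | e | Volunteer bias (g/day) | Pooled bias (g/day) | Pooled bias as % of 0.7 |
|---|---|---|---|---|---|---|
| Low | 0.20 | 0.10 | 0.7 | 0.07 | 0.014 | 2% |
| Middle | 1/3 | 0.30 | 0.7 | 0.21 | 0.07 | 10% |
| High | 0.50 | 0.50 | 1.0 | 0.50 | 0.25 | 36% |

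The bias is zero if d or e is zero. With both positive, it exaggerates the reduction.

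**4. Objective 2.** Baseline level is untouched, because no intervention existed in 2011. Only the comparison of change is affected.

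**The case against.** The best case for the plan has five parts.

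- **Sites.** No site is named in either section. A reader might infer that recruitment and delivery share the very same sites. In a town of about 20,160 that is plausible for the shopping areas, but the text does not say it. A booth timetable is also fieldwork detail that an article may leave out.
- **Exposure.** A reader might go further and infer that booth recruits are bound to be more exposed. The recruitment booth is described as giving information about taking part, not as handing out tools. Delivery is town-wide, and randomly sampled adults use the main shopping areas too.
- **Composition.** The same venue types serve both surveys, so the kind of person who visits them is partly balanced.
- **Detection.** Separate analyses by sample and the follow-up questions on reach would let a reader see divergence.
- **Objective 2.** A volunteer-random gap in change is what that objective sets out to observe.

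Much of this stands. It rules out stating the bias as a fact, and town-wide delivery narrows any exposure gap. It does not remove the risk: like-for-like venues cannot balance an exposure that exists only at follow-up, and separate analyses may reveal a problem without correcting the primary estimate. Nor is this merely omitted detail, since the article itself fixes the venue types, the timing and the estimator. On objective 2, the gap can still be detected; what is limited is its explanation.

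**Conclusion.** The concern holds as a risk, not as a demonstrated bias. Follow-up volunteers may be more exposed than the town as a whole. If they are, and if exposure lowers salt intake, the volunteer contrast and the pooled primary estimate overstate the community effect. Both conditions are needed and the article documents neither.

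The size cannot be derived. Under the assumed inputs the pooled bias is 0.014 to 0.25 g/day salt, or 2% to 36% of the 0.7 g/day design difference, so anything from negligible to material. A reader might pick a wide reach gap and an equal-weight pool of volunteers and random sample alone, and conclude that the effect is overstated by half or more. That is not supported: no reach is given, and such a pool leaves out the paired sub-set, whose members are re-invited by mail and not through a booth.

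For objective 2 the confounding concerns change, not baseline level.

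**What to change.** 1. Keep the same kinds of venue as at baseline, but recruit follow-up volunteers only at sites and times with no intervention booth, workplace session or tool hand-out, and never from an intervention booth.
2. Use the reach questions already in the follow-up survey to compare exposure between the new volunteers and the random sample, and report this beside the results for objective 2.
3. Pre-state a sensitivity analysis of the primary pooled estimate without the new follow-up volunteers, to be read beside the primary result when concluding on the community effect. The unpaired volunteer contrast then drops out. Baseline volunteers who return stay in through the paired sample.

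**Cost.** Some scheduling effort, possibly slower volunteer recruitment, and less precision in the sensitivity estimate. If the sub-set estimates are independent, removing a contrast of weight w widens the interval by a factor of 1/√(1 − w): 1.12 at w = 0.20, 1.22 at w = 1/3 and 1.41 at w = 0.50. No new data are needed.

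**Two alternatives not advised as the fix.** Reweighting volunteers to the random sample's reach would use a self-reported variable that exists only at follow-up, and could itself unbalance the before-after comparison. Making the random contrast primary is a trade-off: it loses precision, and its sampling frame changes from the electoral roll to the telephone directory.
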